#### Parent wellbeing:

- Increased depressed mood
- Increased anxiety/stress
- Increased tiredness/fatigue
- Increased/decreased sleep

STEPS is a psychological intervention, not pharmacological, and so physical adverse reactions are not expected. Medical adverse events will be recorded using standard medical definitions.

### **21.4 Progression Criteria / Stopping Rules**

The study will include an internal pilot study (the first 9-months of recruitment). There are no formal statistical stopping rules; progression rules for the internal pilot are described in Table 4 below. The trial may be prematurely discontinued by the Sponsor or Chief Investigator based on new safety information or for other reasons given by the DMC or PSC regulatory authority or ethics committee concerned.

Another reason for stopping the trial prematurely would be poor recruitment and engagement with the STEPS intervention or attrition during the pilot phase, which does not improve despite efforts to engage clinical teams and parents of referred children. This will be reviewed after the 9-month internal pilot. If the

The electronic version of this document is the latest version. It is responsibility of the individual to ensure that any paper material is the current version. Printed material is uncontrolled documentation.

internal pilot targets for recruitment, engagement or attrition are not met (below), the trial may be terminated on consensus advice of the PSC, DMC and the study funder.

The objective of the internal pilot is to determine whether recruitment, engagement with the intervention and retention to the trial are sufficient to allow the trial to progress and provide a definitive answer on the effectiveness of the intervention. Progression rules regarding recruitment, treatment engagement and attrition during the internal pilot are specified in Table 4. Briefly, green means that the trial will continue, amber – the research team will review ways of improving with the PSC and the Patient and Public Involvement (PPI) Steering Group. The decision to continue or stop the trial will be made independently by the PSC taking advice from the DMC.

Table 4. OPTIMA RCT internal pilot progression rules.

| RECRUITMENT                                                                                                                                                                                                                                                                                                                                                                                   |
|-----------------------------------------------------------------------------------------------------------------------------------------------------------------------------------------------------------------------------------------------------------------------------------------------------------------------------------------------------------------------------------------------|
| 
GREEN: > 70% of recruitment target for that period.
 
AMBER: 50-70%. Lower rate would be also acceptable, if there's an evidence of an upward recruitment trajectory and/or a clear plan for further improvement (e.g., new sites, or ways of recruiting).
 
RED: < 50% and no evidence of an upward trajectory.
                                  |
| INTERVENTION ENGAGEMENT                                                                                                                                                                                                                                                                                                                                                                       |
| 
GREEN: > 90% of participants providing primary outcome data at primary endpoint (3 months post-randomisation) will have engaged with the two first modules of the intervention.
 
AMBER: 60-90%. Lower rate also acceptable if evidence of improvement or/and a clear plan for improving engagement.
 
RED: < 60% and no evidence of improvement.
 |
| ATTRITION                                                                                                                                                                                                                                                                                                                                                                                     |
| 
GREEN: > 75% of participants who have reached the relevant time window will have completed primary endpoint assessments to provide primary outcome data.
 
AMBER: 50-75%. Lower rate acceptable, if evidence of improving retention and/or clear plan for enhancing retention.
 
RED: <50% and no evidence of improving retention.
                |

## 22. Auditing

Auditing is not applicable to this protocol.

## 23. Ethics & Regulatory Approvals

The trial will be conducted in compliance with the principles of the Declaration of Helsinki (1996), the principles of GCP and in accordance with all applicable regulatory requirements.

The research team and the sponsor will submit the study protocol, participant information sheet, consent form, and other relevant supporting documents to the North West - Liverpool Central Research Ethics Committee Research Ethics Committee (REC) and will ensure these have been approved by the appropriate regulatory bodies, prior to any participant recruitment. The protocol and all agreed substantial protocol amendments will be documented and submitted for ethical and regulatory approval prior to implementation.

No recruitment activity will take place before ethical approval for the study has been obtained. The CI and the sponsor will ensure that the main REC is notified that the study has finished within the appropriate timeframe. If the study is terminated prematurely, the REC will be notified within 15 days of the end of the study. The Chief Investigator will submit a final report at conclusion of the trial to the funder, the REC and the Sponsor.

## **24. Protocol amendments**

In case of new information becoming available, which may result in significant changes to the risks and benefits of taking part, the Participant Information Sheet and informed consent form will be reviewed and updated accordingly. All participants actively enrolled in the study will be informed of the updated information and will be given a revised copy of the Participant Information Sheet and informed consent form to confirm their wish to continue taking part.

## **25. Consent**

Participants in the study will be parents of children, who screened positive for high levels of hyperactivity/impulsivity, inattention, and conduct problems, children themselves (optional), and clinicians (qualitative interviews).

### **25.1 Parents**

All participants will provide written informed consent to take part in the study. The informed consent form will be provided in electronic form using Red Pill ePRO system to be completed by the participant before they enter the study. A link to the electronic consent form will be emailed or texted to parents who wish to enrol in the study. The electronic consent form will include a link to the Parent Information Sheet. After answering consent questions, the participant will type in their name and provide a signature. The signature panel works with a mouse or touchscreen. On the consent form there will be a separate question asking parents to consent to a qualitative interview. Parents who do not consent to this will not be invited to take part in the interviews. Parents, who agree to take part in the interviews via the written consent form, will be asked to confirm their consent verbally before the interview takes place.

On submitting the signed consent form the participant is shown the form within Red Pill with their completed answers and signature. They are asked to check the box to make the declaration that they will electronically sign the consent on saving the form. On saving the form a time stamped PDF version of the consent form is created and stored in the system. It is also sent to the participant by email as a record of their consent. A copy of the completed form will be extracted by a research assistant and retained at the study site and placed in central file. A copy of the consent form will be shared with the child's clinical team and a child's GP will be informed of the study participation.

### **25.2 Children**

Parents will provide consent on behalf of the children to take part in ESO (remote drawing task). Consent statements regarding a child's participation in the study will be included in the electronic form completed by

The electronic version of this document is the latest version. It is responsibility of the individual to ensure that any paper material is the current version. Printed material is uncontrolled documentation.

parents via the Red Pill ePRO system. Parents will be emailed a Child Information Sheet when they are invited to participate, and they will be asked to share it with their child. Children's verbal assent will be obtained prior to completing the remote drawing task. We will not ask the children to provide written assent as the burden associated with the task is low. It is a drawing game completed with a parent in the comfort of a family home. Moreover, collecting children's assessment electronically will be challenging due to a young age of participants. Researchers will record child's verbal responses to assent questions on the assent form, sign the form and email to the parent for their record. Child's verbal assent will also be documented in the trial database.

### **25.3 Clinicians**

All participants will provide written informed consent to take part in the study. The informed consent form will be provided in electronic form using Qualtrics. A link to the electronic consent form will be emailed to clinicians, who wish to take part in the interviews. The electronic consent form will include a link to the Clinician Information Sheet. After answering consent questions, the participant will confirm their consent by typing in their name in the response box. A copy of the completed consent form countersigned by the researcher will be emailed to the clinician and also retained at the study site and placed in the central study file.

### **25.4 Withdrawal of participants**

We do not expect using STEPS to lead to harm that would suggest the intervention needs to be discontinued. However, parents will be able to withdraw from the trial at any point for any reason. Through the information sheet, parents will be informed that they can withdraw from the study either by informing the team that they wish to opt out of taking part in follow-ups or by ignoring the reminders to complete the follow-up surveys. They can also stop using STEPS and delete the app from their phone at any time.

If a participant actively informs the research team that they would like to withdraw from the study, it will initially be clarified which aspects of the study they wish to withdraw (i.e., intervention, data collection or data collection from records) from and they will then be sent a 'confirmation of withdrawal' email and will be entered in the Red Pill database as withdrawn from the study. Copy of the email confirming withdrawal will be retained in the trial master file. Information about withdrawal will be shared with the participant's local clinical team. Participants will be made aware in the participant information sheets that any non-identifiable data collected up to the point of their withdrawal may still be used in the analyses. After withdrawal has been confirmed, participants will not be requested to complete any further measures but will be asked by the research team to provide voluntary feedback regarding the reason for their withdrawal. If feedback is provided, this will be recorded in the database. Once a participant has withdrawn from the study it will not be possible to re-enter the study or resume using the app. Withdrawn participants will not be replaced into the study.

Participants will not be withdrawn from the study due to poor engagement with the app. If a participant does not continue using STEPS, we would still invite them to complete outcome measures unless they explicitly state they wish to withdraw. In this case participants will be informed it is still key to the success of the study to collect outcome measures, even if they do not want to use the app.

Failure to complete outcome measures at one follow-up time point will not imply withdrawal from the study, and the participants will still be invited to complete measures at the next follow-up time point, unless they explicitly state otherwise.

## **26. Confidentiality**

In this study we will collect the following identifiable information: names, dates of birth, postal address, telephone number and email address. The STEPS app will collect administrative data (i.e., name, email address, mobile phone number), required to enable participants to access the STEPS app and to notify them about the updates.

The Chief Investigator and all members of the research team will take every effort to preserve the confidentiality of participants taking part in the study. To de-identify the data, each participant will be assigned a study ID. A reference file with the study IDs and participant identifiable information will be kept in a secure King's College OneDrive for Business folder, which is a Microsoft 365 integrated cloud-based storage and will be backed up on an external encrypted hard drive.

Participants identifiable data required for administrative purposes (e.g., name and contact details) will be stored in a separate file from the data files. These will be accessed only by those members of the research team who are responsible for contacting participants (e.g., to email a link to the online survey). No individual participant's data will be identifiable in the publications or reports that may result from this study. All personal data will be stored securely for seven years in line with the KCL record retention policy.

## **27. Publication Policy**

A full and complete account of the trial results will be published in a high-quality peer reviewed scientific journal and full report for the funder. Authorship will be determined according to COPE standards based on the individual contributions. In addition, the findings will be disseminated through oral and poster presentations at a range of conferences and seminars in the UK and overseas. There will also be a general dissemination programme for clinicians, commissioners and parents through the OPTIMA website.

## **28. Insurance / Indemnity**

The lead sponsor, King's College London, will take primary responsibility for ensuring that the design of the study meets appropriate standards and that arrangements are in place to ensure appropriate conduct and reporting. King's College London also provides cover under its No Fault Compensation Insurance, which provides for payment of damages or compensation in respect of any claim made by a research subject for

The electronic version of this document is the latest version. It is responsibility of the individual to ensure that any paper material is the current version. Printed material is uncontrolled documentation.

bodily injury arising out of participation in a clinical trial or healthy volunteer study (with certain restrictions). The co-sponsor, South London and Maudsley NHS Foundation Trust, takes responsibility for ensuring that appropriate standards, conduct and reporting are adhered to regarding its facilities and staff involved with the project.

## 29. Financial Aspects

The study has been funded by the NIHR reference number RP-PG-0618-20003. The project funding covers all costs in relation to the OPTIMA programme, including but not limited to, higher education institutions costs, equipment and PPI cost. The funding covers the period from 1 March 2020 to 30 September 2025.

## 31. Appendices

### APPENDIX 1

#### OPTIMA Assessment & Diagnosis Form

#### 1. Has the child been formally assessed by the services they were referred to?

Yes (go to question 2)

No (end of form)

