## **9.4 Comparator Arm: Wait As Usual (WAU)**

No alternative evidence-based intervention is currently recommended, available, or implemented in the United Kingdom during the post-referral waiting period for patients waiting for a child health services assessment. WAU, therefore, is the most appropriate comparator. Those randomized to WAU will receive STEPS after they have completed the 12-month follow-up. In the sites across our three centres, we do not expect any patients to receive their clinical assessment and initiate treatment within the first three months of randomisation (T2) or few - if any - patients to engage in self-initiated treatment during this period. Parents will not be stopped from initiating their own access to services over the 12 months of the trial. All treatments received will be carefully recorded throughout the trial through the Child and Adolescent Service Use Schedule (CA-SUS; Barrett et al., 2012) and the Assessment & Diagnosis form (see Appendix 1).

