### **10.3.5 Clinical diagnosis**

*Risk ratio at T5 as exploratory outcome.*

Information about ADHD diagnosis will be extracted from medical records at 12-month follow-up and recorded on the Assessment & Diagnosis form (Appendix 1). In case it is not possible to access a child's medical record, information will be collected directly from a parent (via a phone call). A presence of ADHD diagnosis will be coded as 1 and absence as 0. In addition, if other diagnosis has been given, information about the type of diagnosis will be recorded for descriptive purposes.

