### **10.3.6 Pharmacological treatment**

*Risk ratio at T5 as exploratory outcome.*

Information about any pharmacological treatment for neurodevelopmental and mental health disorders will be extracted from medical records at 12-month follow-up and will be recorded on the Assessment & Diagnosis form (Appendix 1). In case it is not possible to access a child's medical record, information will be collected directly from a parent (via a phone call). A presence of pharmacological treatment will be coded as

1 and absence as 0. If pharmacological treatment has been prescribed, information about the name of the drug and dose will be recorded for descriptive purposes.

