#### 2. Date of assessment: dd/mm/yyyy

**3. Following their assessment, has the child received an ADHD diagnosis from the service they were initially referred to?**

Yes (go to question 4)

No (go to question 6)

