**6. Has the child received treatment?**

No treatment

Yes, medication (Go to Q7)

Yes, psychological treatment for the child

Yes, parenting support

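### The Appendix 1 form is narrower than the 12-month outcomes it records: an ADHD diagnosis made outside the referred service cannot be entered, and the form stops for children that service has not assessed

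*Protocol*

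**What the plan says.** **Outcome definitions.** Section 10.3.5: "Information about ADHD diagnosis will be extracted from medical records at 12-month follow-up and recorded on the Assessment & Diagnosis form", and "A presence of ADHD diagnosis will be coded as 1 and absence as 0". Section 10.3.6: "Information about any pharmacological treatment for neurodevelopmental and mental health disorders will be extracted from medical records at 12-month follow-up", recorded on the same form and also coded 1 or 0. Neither section limits the outcome by service, nor does exploratory objective 5 in section 5.3. A parent is telephoned only when the child's record cannot be accessed. Section 19.1 plans a relative risk, STEPS against WAU, for each outcome by modified Poisson regression.

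**The form (Appendix 1).** Question 1 asks: "Has the child been formally assessed by the services they were referred to". Yes leads on; No ends the form. Question 3 asks: "has the child received an ADHD diagnosis from the service they were initially referred to". Its negative answer is routed "No (go to question 6"). Question 6 asks "Has the child received treatment" and names no service; question 7 takes the drug and dose.

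**Care outside the referred service.** Section 9.4: "Parents will not be stopped from initiating their own access to services over the 12 months of the trial". It adds that treatments received are recorded through both the CA-SUS and this form.

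**The concern.** The form is the named instrument for both outcomes, but it asks a narrower question than the outcome definitions do. The difference falls on care obtained outside the referred service, which the protocol expects to be possible. Section 9.4 permits it for the whole 12 months, and objective 4 in section 5.3, with section 19.2, plans an analysis of contact with such services. Section 4 cites delays of up to 200 days to initial assessment, and section 9.4 expects no clinical assessments in the first three months. Some children may therefore still be unassessed at T5.

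At stake is the meaning of two reported relative risks. They would be presented as the effect of STEPS on receiving a diagnosis and on being prescribed medication by 12 months, while the form measures something closer to events reached through one service's own assessment.

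**Working it through.** **1. The plan's own figures.** The protocol gives no event rate and no power for diagnosis or medication. Its only power figure is N = 352 for the primary outcome, and it reproduces. With d = 0.4, two-sided alpha 0.05 and 90% power (section 13), n per arm = 2 × (1.960 + 1.282)² / 0.4² = 131.3, rounded up to 132. Then 132 / 0.75 = 176 per arm, 352 in total. The present point does not touch that figure.

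**2. Routes through the form.** Each possible true state, followed through the printed routing:

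| Assessed by referred service (question 1) | True ADHD diagnosis | Question 3 | Medication (questions 6 and 7) |
|---|---|---|---|
| Yes | From referred service | Yes | Recorded, any source |
| Yes | From elsewhere only | No | Recorded, any source |
| Yes | None | No | Recorded, any source |
| No | From elsewhere | Not reached | Not reached |
| No | None | Not reached | Not reached |

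Three results follow.
- A diagnosis made elsewhere is never entered as present. The answer is No in row 2 and blank in row 4.
- Medication is lost only in the two rows where question 1 is No. In the other three, question 6 carries no service limit, and a No at question 3 still leads to it.
- Where question 1 is No, both outcomes are blank. The protocol does not say whether a blank becomes 0 or missing.

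**3. What each treatment of an ended form implies.**
- Coded 0: true events among these children count as non-events, so absolute rates are understated wherever outside care occurred.
- Treated as missing: the outcomes exist only for children assessed by the referred service by 12 months. That subset is defined after randomisation, which sits badly with the intention-to-treat principle in section 19.1.

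**4. Effect on the relative risk (assumed rates; ended forms coded 0).** Let p1 and p0 be the true risks in STEPS and WAU, and s1 and s0 the fractions of true events the form captures. Recorded RR = (p1 × s1) / (p0 × s0). With assumed p1 = 20% and p0 = 30%, true RR = 20/30 = 0.67.

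| s1 (STEPS) | s0 (WAU) | Recorded risks | Recorded RR |
|---|---|---|---|
| 90% | 90% | 18% / 27% | 0.67 |
| 70% | 70% | 14% / 21% | 0.67 |
| 90% | 70% | 18% / 21% | 0.86 |
| 70% | 90% | 14% / 27% | 0.52 |

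Equal capture leaves the RR unchanged and costs power only. In a two-proportion normal-approximation test at two-sided 5% with 176 per arm, capture of 100, 90, 80 and 70% in both arms gives power of 58, 53, 47 and 41%. Unequal capture moves the RR either way.

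**5. Where the effect lies.** All rates below are assumed percentages of the whole arm, with the outside events being those the form misses.
- Effect only in outside care: referred-service route 15% in both arms, outside route 5% in STEPS and 10% in WAU. True RR = 20/25 = 0.80; recorded RR = 15/15 = 1.00.
- Effect only in the referred-service route: 10% against 15%, with 5% outside in both arms. True RR = 15/20 = 0.75; recorded RR = 10/15 = 0.67.

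The first moves the RR towards 1, the second away from it.

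**The case against.** Several points can fairly be made for the plan.

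*Medication is mostly safe.* A reader might infer that any outside prescription is lost. The form does not support that. Question 6 is open to any source, so the loss is confined to children with No at question 1. The CA-SUS also collects prescribed mental health medication at every time point (section 10.4.1, Table 2). This stands and narrows the point. However, section 10.3.6 does not name the CA-SUS as a source for this outcome, and its stated medication item does not supply the diagnosis outcome.

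*A blank is not a zero.* A reader might infer that ended forms are coded as absent. That is a natural reading of 1/0 coding but is not stated, and the derivation may properly be left to the SAP. This stands as to the wording. It does not remove the problem, because an analysis rule cannot recover information the form never asked for, and treating the blank as missing brings the subset problem in step 3.

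*The direction of bias is unknown.* A reader might infer that the relative risks are pulled towards 1. Steps 4 and 5 show that this depends on which arm's events are missed and where any effect lies, and the protocol gives no rates with which to decide. The objection stands in full.

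*The limit may be deliberate, or the medical record may show outside care.* Sections 10.3.5 and 10.3.6 do not state a limit to one service. Even if the record does show outside care, question 3 has no answer that enters an outside diagnosis as present.

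*The outcomes are exploratory.* True, and it bounds the importance.

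**Conclusion.** The form and the outcome definitions disagree and need to be reconciled. It follows from the text alone that an outside ADHD diagnosis cannot be entered as present, and that neither outcome is recorded for a child not assessed by the referred service. The size of the effect cannot be derived from the protocol. It depends on how many children remain unassessed at 12 months, how much outside care they obtain, whether that differs by arm, and how ended forms are coded. The relative risks in the working rest on assumed rates and show only that the bias may be nil or go in either direction. Understated absolute rates follow only if blanks are coded 0.

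The scope is exploratory objective 5 alone. The primary outcome, the secondary outcomes and N = 352 are unaffected. The correction is worth making because it is cheap and settles what two reported relative risks measure.

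**What to change.** In Appendix 1:
- Route No at question 1 on to the diagnosis and treatment items (questions 3, 6 and 7) instead of ending the form.
- Reword question 3 to ask about an ADHD diagnosis from any service, and add a field for which service made it.

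In section 10.3.6, name the CA-SUS medication item, already collected, as a cross-check for the medication outcome. It should be a check rather than a replacement: its stated scope is mental health conditions, whereas the outcome also covers neurodevelopmental disorders.

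Alternatively, if the referred service alone is intended, restate the outcomes in sections 10.3.5 and 10.3.6 and in objective 5 with that limit. Question 6 would then need the same limit. If any early exit from the form is kept, state how an ended form is coded.

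The cost is a routing and wording edit, with no extra visit. The small downside is that some information on outside care will be parent-reported.
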